### Surgical intervention

All patients will be operated by the authors MA or JW, who both have extensive experience in cervical spine surgery and this ACDF technique. The patients will be positioned supine with their neck in neutral position or slightly extended under general anaesthesia. The affected cervical disc level will be verified with fluoroscopy. A small transverse incision will be made on the right side. Medial to the carotid sheath, the pre-vertebral space will be opened and the anterior cervical spine will be exposed. Caspar spreader and 2 distraction pins will be placed in the affected segment. A standard anterior discectomy with the aid of loupe magnification or microscope (depending on the surgeon’s preference) will be performed in all cases. The posterior longitudinal ligament will be opened and the nerve root and dura will be decompressed adequately. Once the anterior discectomy has been performed, a PEEK interbody cage (Medicrea Manta, Lyon, France) (group 1) filled with local bone[20] obtained from removal of osteophytes, or the Valeo C+CSC spacer (Amedica Corporation, Salt Lake City, Utah) (group 2) will be placed within the intervertebral space under fluoroscopic guidance. The CSC core should be smeared with blood obtained by scratching the end plate after the disc space is prepared. No supplemental fixation (e.g., cervical plate) will be used in the procedure. If required, a vacuum drain will be placed and the wound will be closed in layers.

### Outcome assessment

Baseline assessments include demographics, work status, smoking status, neck and arm pain, history of neck trauma, medical history, pain medication, body mass index, and neurological signs and symptoms. A general physical and neurological examination is performed before the patient is enrolled into the study and will be repeated at each subsequent visit.

We will assess the below described validated outcome parameters. Patients will not be informed about their previous scores. Follow-up examinations will take place by the surgeon at 3 months, 6 months, 12 months, and 24 months after randomization. The schedule of follow-up visits, radiographic studies and outcomes measures is included in Table 2. The following measures of outcomes will be used:

1) Neck Disability Index (primary outcome measure): The NDI is a patient-completed 10-item questionnaire on 3 different aspects; pain intensity, daily work related activities and non-work related activities. Each item is scored from 0 to 5 and the total score ranges from 0 (best score) to 50 (worst score). The NDI is a modification of the Oswestry Disability Index and has been shown to be reliable and valid for patients with cervical pathology [21,22] and has been validated in the Dutch language [23].

2) Short-Form 36 (SF-36): The SF-36 [24] is a generic health status questionnaire that can easily be filled out by the patient at home. The questionnaire consists of 36 items on physical and social status of the patient subdivided in 8 domains; 1) physical functioning, 2) physical restrictions, 3) emotional restrictions, 4) social functioning, 5) somatic pain, 6) general mental health, 7) vitality and 8) general health perception. The questions are scored on a scale of 0 (worst health) to 100 (ideal health). This questionnaire has been used frequently and is validated in surgical studies on spine pathology [25,26].The Dutch language version has also been validated [27].

3) Pain intensity, measured by Visual Analogue Score (VAS) of arm and neck. The VAS of arm pain will measure the experienced pain intensity in the arm during the week before visiting the researcher. Pain will be assessed on a horizontal 100 mm scale varying from 0 mm (no pain) to 100 mm (worst pain imaginable). Patients do not see the results of earlier assessments and will score the pain experienced at the visit. Since many patients with radicular arm pain have neck pain as well, we will also measure the intensity of solitary neck pain. Reliability, validity and responsiveness of VAS have been shown [28].

4) Perceived recovery: Likert Scale is a 7-point scale measuring the perceived recovery, varying from ‘complete recovery’ to ‘worse than ever’. This outcome scale has been used in previous studies and has been shown to be valid and responsive to change [29]. “Complete recovery” and “almost complete recovery” are defined as good result.

5) Radiological outcome: Anterior/posterior, and lateral views of the cervical spine will be performed at each visit. Displacement or subsidence of the device will be assessed by using the lateral radiograph. Only a change of >3 mm will be considered clinically significant due to the margin of error in radiographic determination of displacement distances. Radiolucency at the cage-bone interface will be assessed as either present (if extending 50% of the length of the cage) or absent using a standard lateral radiograph. To verify fusion, CT axial images at 2 mm slices will be taken at the 6 months visit only.

6) Other outcome measures: In addition to the outcomes measures, data will be captured on details of the surgical procedure and hospitalization such as type and size of implant, duration of surgery, estimated blood loss, operative and postoperative complications, day of mobilization, and duration of hospitalization. Adverse events and reoperations will also be recorded by the operating surgeon.

**Table 2 T2:** Data collection and outcome measures

**Measure**	**Pre-Op**	**Intra-Op**	**3 months**	**6 months**	**12 months**	**24 months**
Inclusion / exclusion criteria	x					
Product use, operative time, blood loss		x				
Neurological examination	x		x	x	x	x
Neck Disability Index, Arm Pain VAS, Neck Pain VAS, SF-36, Recovery Likert	x		x	x	x	x
Radiographs X-ray	x		x	x	x	x
CT scan				x		

The de-identified data from the initial visits, hospitalization and follow-up visits are entered by research nurses and physician assistants into a database via an Electronic Data Capture system (Acumen Healthcare Solutions, LLC, Plymouth, Minnesota, USA). Hospital staff schedules follow-up visits and supervises the collection of the patient-completed data forms. The source documents are kept filed in the hospitals where the procedures are performed.

Participating patients are given a small stipend to cover travel costs for follow-up visits. The cost of the procedure (including the interbody fusion devices) is covered by the patient’s health insurance, but the expense of extra imaging and radiologist fees are paid by the study sponsor.

### Sample size and data analysis

Sample size for this equivalence trial has been established using power analysis incorporating data from journal article reports of similar ACDF studies. For sample size calculations, we have used the change in NDI from pre-op to one year post-op cited in the literature for ACDF with carbon fiber reinforced PEEK cages: 10% reduction (improvement) with a standard deviation of 22% [30]. The Minimal Clinically Important Difference (MCID) for the NDI is 7.5 points or 15% [31], which is the equivalence interval for sample size calculation. A 46-patient Valeo C enrollment has a power of .90 when compared with a PEEK study arm of the same size. Incorporating a one-year estimate of 8% loss to follow up, a total of 100 patients need to be enrolled.

The statistical significance of categorical data such as fusion will be tested using the Pearson Exact test. Parametric data will be evaluated using the Student’s t-test. The first data analysis will be performed when all of the 1-year follow-up data is available for the primary endpoint. The two groups will be considered equivalent if the mean NDI improvement for the silicon nitride cage group is within a range from the mean of the PEEK group minus the NDI MCID to the PEEK mean plus the MCID. A repeated measurements analysis of variance for the primary outcome measure will also be performed in order to compare the evolving patterns over time.

The inclusion period started in December 2011 and 2-year follow-up measures will be completed by the end of 2014.

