**Figure 2 F2:**
[figure not shown]
Silicon nitride, titanium, PEEK and trabecular metal imaging characteristics in a human cadaveric vertebra (unpublished data).

The Valeo C+CSC cage has received the CE Mark based on preclinical testing and standards compliance, but has not been evaluated in a clinical study. Good clinical practice means that every new device should be compared to the golden standard prior to implementation of the device on a large scale. Therefore, it is necessary to perform a randomized controlled effectiveness trail on Valeo C+CSC versus PEEK cages. In the CASCADE (CAncelous Structured Ceramic Arthrodesis DEvice) trial, we will randomly and blindly compare anterior discectomy with ceramic cages versus anterior discectomy with PEEK cages. In this equivalence trial, we hypothesize similar effectiveness and no difference in clinical improvement between the ceramic cage and the PEEK cage as measured with the Neck Disability Index (NDI). Moreover, radiological properties will be documented focusing on fusion and subsidence.

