Although there is no consensus on which interbody device to use, currently PEEK cages are considered as the golden standard for anterior cervical discectomy with fusion by many surgeons [15-19]. However, PEEK and titanium have some undesirable imaging characteristics that result in a demand for better cages with similar effectiveness. Figure 2 illustrates the superior imaging properties of MC^2^ ceramic material compared to PEEK, titanium and trabecular metal. Moreover, the CSC material fills the center hole for the purpose of providing a scaffold for bone ingrowth resulting in solid fusion and no subsidence of the cage. The CSC form of the material has performed well in an animal model [37] but the results and effectiveness need to be validated in humans. It is possible that solid fusion without signs of subsidence may lead to improved clinical outcome.

The present protocol of the CASCADE trial is designed to demonstrate the effectiveness and security of cancellous structured ceramic cages compared to the golden standard PEEK cages in patients treated with anterior cervical discectomy and fusion. Worldwide implementation of new devices should only be done after completion of randomized controlled trials. In our opinion, Level 1 evidence that government and health insurance organizations are demanding would not be possible without close cooperation between industry and researchers, but transparency is warranted and relevant conflicts of interest must be disclosed.

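### The 15% equivalence margin exceeds the 10% improvement planned for PEEK, so meeting it cannot by itself support a claim of similar or demonstrated effectiveness

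*Protocol article*

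**What the plan says.** All the figures are in the protocol article, section Sample size and data analysis, unless noted.

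- Expected pre-operative to one-year change with PEEK: "10% reduction (improvement) with a standard deviation of 22" per cent.
- Margin: "The Minimal Clinically Important Difference (MCID) for the NDI is 7.5 points or 15% [31], which is the equivalence interval for sample size calculation".
- Decision rule: the groups are equivalent if the mean ceramic improvement is "within a range from the mean of the PEEK group minus the NDI MCID to the PEEK mean plus the MCID". No confidence interval is named, and no other condition requires the ceramic arm to improve.
- Size: "A 46-patient Valeo C enrollment has a power of .90 when compared with a PEEK study arm of the same size", and "Incorporating a one-year estimate of 8% loss to follow up, a total of 100 patients need to be enrolled".
- Scale (Outcome assessment, item 1): "the total score ranges from 0 (best score) to 50 (worst score"), so 7.5 points is 15% of the range.

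The intended conclusions are wider than the rule. The Background, after Figure 2, states: "In this equivalence trial, we hypothesize similar effectiveness and no difference in clinical improvement between the ceramic cage and the PEEK cage". The Discussion says that the trial is "designed to demonstrate the effectiveness and security of cancellous structured ceramic cages compared to the golden standard PEEK cages".

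**The concern.** The margin is justified only as the MCID. It is never set against the 10% improvement given in the sentence before it. An MCID describes a change that matters to a patient; it does not guarantee that a new device keeps any of the improvement seen with the comparator. When the margin is larger than that improvement, the equivalence result and the claim of effectiveness come apart: the first can be met while the second is false.

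This matters because the Background says that the ceramic cage has had no clinical evaluation, and the trial is presented as the evidence on which wider use would rest. If PEEK improvement turns out as small as planned, a result labelled as similar effectiveness could not rule out that all of it had been lost.

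**Working it through.** **Inputs.** PEEK improvement 10%, SD 22%, margin 15%, 46 evaluable per arm, 8% loss, all from Sample size and data analysis. All percentages are read as percentages of the 0–50 scale, as the article itself does in equating 7.5 points with 15%. If the 10% were relative to baseline, it would be less than 5 points and the gap would widen. The significance level is not stated; one-sided 5% per test (a 90% interval) is assumed, with one-sided 2.5% as the other end of the range.

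**1. The plan's own figure.** Two one-sided tests, true difference 0:

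n per arm = 2 × [22 × (1.645 + 1.645) / 15]² = 46.6

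SE of the difference = 22 × √(2/46) = 4.59% (2.29 points)

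Power at 46 per arm = 2Φ(15/4.59 − 1.645) − 1 = 0.896

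This agrees with 46 and 0.90. Loss: 46/0.92 = 50 per arm, 100 in all. The sample size is reproduced, and it uses the SD and the margin; the 10% does not enter. At one-sided 2.5% the power would be 0.81, which does not match.

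**2. Margin against expected improvement.** 15/10 = 1.5. The zone for the ceramic mean is 10% ± 15% = −5% to +25%, or 5 ± 7.5 = −2.5 to +12.5 NDI points. Zero lies inside.

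**3. Chance of declaring equivalence when the ceramic arm truly does not improve** (normal approximation, SE 4.59; the negligible upper-limit term is left out of the formulas).

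With PEEK at 10%, the true difference is −10%:
- Means compared, as written: Φ((−10 + 15)/4.59) = Φ(1.09) = 0.86.
- 90% interval within ±15%: the observed difference must lie above −15 + 1.645 × 4.59 = −7.45, so Φ((−10 + 7.45)/4.59) = Φ(−0.555) = 0.29.
- 95% interval: the limit is −6.01, giving Φ(−0.87) = 0.19.

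The same steps with PEEK at 20% give the second row:

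| True ceramic / PEEK | Means compared | 90% interval |
|---|---|---|
| 0% / 10% | 0.86 | 0.29 |
| 0% / 20% | 0.14 | 0.003 |

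**4. A single observed result.** With t on 90 degrees of freedom the 90% half-width is 1.662 × 4.59 = 7.6%. Observed means of 0% and 10% would give −17.6% to −2.4%, which fails the interval rule. With PEEK observed at 10%, the ceramic mean would need to be at least 10 − (15 − 7.6) = 2.6%.

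**5. Would a tighter margin do?** By the formula in step 1, a 10% margin needs 105 per arm (115 after 8% loss), and 46 per arm has power of about 0.41. A 5% margin needs 420 per arm (457 after loss), and 46 per arm has none.

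**The case against.** An MCID margin is conventional, cited and fixed in advance on the primary scale, and the sample size follows from it. That stands: neither the calculation nor the use of an MCID is an error in itself.

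The 10% drives neither the sample size nor the decision rule, which uses the observed PEEK mean. That also stands, and it makes the point conditional. With PEEK at 20%, a ceramic arm without improvement passes an interval rule in 0.3% of trials.

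Three stronger readings are tempting, and the document does not support them.

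- *The margin lets a useless cage through in 86% of trials.* That figure belongs to the comparison of means without an interval. Only the 29% (19% with a 95% interval) is due to the margin.
- *The benefit of the cage could be lost entirely.* The 10% is a change from before surgery to one year. Both arms have the same discectomy and decompression (Surgical intervention), and the Discussion says that earlier trials suggest fusion may not always be needed. A ceramic arm at 0% would have lost the whole improvement seen with PEEK, which is an extreme case and not the same as losing the cage's own contribution.
- *The 10% is wrong.* It does put the average PEEK patient below the MCID (5 against 7.5 points), so the figure merits a look at its source. That source is not available here, and nothing in the article shows it to be mistaken.

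**Conclusion.** The point holds as a limit on what the trial may conclude. On the stated planning figures the margin is 1.5 times the expected control-arm improvement, and the zone of −5% to +25% includes no improvement. A true 0% against 10% would be declared equivalent in about 29% of trials under a 90% interval rule. This rests on a 10% PEEK improvement, an SD of 22%, 46 evaluable patients per arm, and an assumed one-sided 5% level. It disappears if PEEK improves by clearly more than 15% (7.5 points).

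It does not follow that the margin must be narrowed or the trial enlarged. What does follow is that meeting the rule shows that a difference above 7.5 points is unlikely, and no more, unless PEEK itself is seen to improve by clearly more than that. This should be fixed, but it does not invalidate the design.

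**What to change.** Keep 100 patients and the 7.5-point margin. In Sample size and data analysis, amend the decision rule as follows.

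1. Equivalence is met when the confidence interval for the difference in mean one-year NDI improvement lies wholly within ±7.5 points. The interval level is to be stated; 90% fits the planned power.
2. Meeting it is reported as: *a difference larger than 7.5 NDI points is excluded*.
3. The interval is always shown beside the observed PEEK improvement.
4. Similar effectiveness, or demonstrated effectiveness, is concluded only if the observed PEEK improvement clearly exceeds 7.5 points. The meaning of clearly should be set beforehand. One option is a lower 90% confidence limit for the PEEK mean above 7.5 points: with SE 22/√46 = 3.24% (1.62 points), this needs an observed PEEK mean of about 7.5 + 1.645 × 1.62 = 10.2 points.

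The hypothesis in the Background and the aim in the Discussion should be brought into line with this.

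Improvement within the ceramic arm may be reported descriptively. It should not be a second required test: it is an uncontrolled before-after comparison that decompression alone could satisfy, and it does little against a partial loss. A true ceramic 10% against PEEK 20% has the same −10% difference as in step 3, so it passes the interval rule in about 29% of trials, and the extra test leaves that rate essentially unchanged.

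The cost is wording only. With the interval rule, power is the 0.896 in step 1, which is what the plan already claims. The downside is a more limited claim if PEEK improvement proves as small as planned.

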### Randomization procedure

In order to eliminate confounding factors, the study is designed as a randomized controlled trial. Patients will be randomly allocated to the Valeo C+CSC or PEEK cages. Randomization will take place in the operating room within 6 weeks after inclusion. A randomization list was prepared by the data manager. A random numbergenerator was used to create the allocation sequence of blocks of 4, 6, and 8 to ensure equal distribution of the randomized treatments. The data manager, who is not involved in the selection and allocation of patients, prepared numbered, coded, sealed envelopes containing the treatment allocation. In the operating room, after induction of anaesthesia, the surgeon will open the next numbered envelope and the allocated treatment will be performed. Patients will be kept blinded for the allocated treatment for 1 year.

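### Cheap improvement for secondary outcomes: the exact test named for yes/no outcomes is valid but conservative; Boschloo's test also holds 5% and keeps more power

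*Protocol article*

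**What the plan says.** Under Sample size and data analysis, one sentence covers all categorical outcomes: "The statistical significance of categorical data such as fusion will be tested using the Pearson Exact test". It does not say whether the test is conditional or unconditional. The article states no significance level, expected event rate or power for any yes/no outcome. Its power statement, "A 46-patient Valeo C enrollment has a power of .90 when compared with a PEEK study arm of the same size", concerns the NDI only.

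Several secondary outcomes are yes/no or are made so by the Outcome assessment section: fusion on the 6-month CT, displacement or subsidence above 3 mm, radiolucency (present or absent), a good result on perceived recovery, reoperations and complications. The Background section gives some of them weight: "radiological properties will be documented focusing on fusion and subsidence".

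**The concern.** A conditional exact test fixes the total number of events and looks only at how they split between the arms. With about 46 patients per arm few splits are possible, so the attainable p-values are coarse. The largest one not above 0.05 is often well below it, and a nominal 5% test then runs at a lower true level. The unused part of the 5% is lost power.

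Boschloo's test uses the same p-value only to rank the tables. It then sets the cut-off so that the rejection probability, maximised over the unknown common rate, stays at or below 5%. The conditional cut-off of 0.05 already meets that condition, so Boschloo's cut-off cannot be lower: it rejects the same tables and usually more. At stake is some avoidable loss of power in comparisons for which the trial was not sized.

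**Working it through.** **Inputs.** From the article: 46 analysed per arm, 100 enrolled, equal allocation in "blocks of 4, 6, and 8 to ensure equal distribution of the randomized treatments". Assumed, because not given: two-sided alpha 0.05, and event rates between 2% and 98%.

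**The plan's own figure.** The inputs are "10% reduction (improvement) with a standard deviation of 22"% and a margin given as "The Minimal Clinically Important Difference (MCID) for the NDI is 7.5 points or 15"%.
- Two-sided 5% formula: n = 2 x (1.960 + 1.282)^2 x 22^2 / 15^2 = 45.2, so 46 per arm, with power 0.905.
- Two one-sided 5% tests, true difference 0: n = 2 x (1.645 + 1.645)^2 x 22^2 / 15^2 = 46.6, with power 0.896 at 46.
- Loss to follow-up: 46 / 0.92 = 50 per arm, 100 in total, as in "Incorporating a one-year estimate of 8% loss to follow up, a total of 100 patients need to be enrolled".

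So 46 per arm with power about 0.90 is reproduced. It serves here only to fix the number per arm.

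**Method for yes/no outcomes.** All 47 x 47 tables were enumerated. The conditional p-value of a table is the sum of the hypergeometric probabilities, given the event total, of all splits at least as extreme. At 46/46 the exact Pearson test and Fisher's test have the same rejection region. Level and power are sums over rejected tables of Bin(x1; 46, p1) x Bin(x2; 46, p2). Boschloo's cut-off, with the level maximised over common rates from 0.001 to 0.999, is a conditional p-value of at most 0.0752.

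**True level at 46/46, %.** By symmetry a rate p and a rate 1 - p give the same level.

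| Common rate | Conditional | Boschloo |
|---|---|---|
| 5% or 95% | 0.6 | 1.9 |
| 10% or 90% | 2.1 | 3.4 |
| 20% or 80% | 2.6 | 4.6 |
| Maximum over all rates | 3.02 | 4.71 |

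**Power at 46/46, %.** The gain is the difference of the rounded figures shown.

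| Rates | Conditional | Boschloo | Gain |
|---|---|---|---|
| 95 v 80 | 49.4 | 56.5 | 7.1 |
| 95 v 75 | 72.1 | 78.1 | 6.0 |
| 90 v 70 | 58.9 | 67.5 | 8.6 |
| 90 v 75 | 37.3 | 45.9 | 8.6 |
| 85 v 60 | 70.9 | 77.6 | 6.7 |
| 80 v 50 | 81.9 | 85.9 | 4.0 |
| 5 v 15 | 23.9 | 30.6 | 6.7 |
| 2 v 15 | 46.7 | 58.4 | 11.7 |
| 2 v 10 | 16.0 | 26.5 | 10.5 |

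That is about 4-12 points.

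**Slightly unequal arms.** Gain of Boschloo's test in percentage points. In the middle columns the first figure applies when the larger arm has the higher rate, the second when the smaller arm has it. The last column spans both.

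| Split | Maximum level, conditional | 90 v 70 | 90 v 75 | 95 v 80 | 2 v 10 and 2 v 15 |
|---|---|---|---|---|---|
| 46/45 | 3.9% | 2.9 / 3.1 | 3.3 / 3.1 | 3.5 / 4.1 | 9.9 to 12.8 |
| 47/45 | 3.8% | 1.5 / 3.3 | 0.8 / 4.2 | 2.2 / 7.9 | 9.8 to 12.9 |
| 48/44 | 3.9% | 2.3 / 4.5 | 2.4 / 4.9 | 2.4 / 5.4 | 4.8 to 8.0 |
| 49/47 | 4.1% | 3.4 / 3.1 | 3.5 / 3.9 | 3.2 / 7.3 | 9.0 to 12.5 |

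That is about 1-8 points for fusion-type rates and 5-13 for rare events. For rates nearer one half the gain can almost vanish: 46.8 to 47.1 for 60 v 40 at 49/47.

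**Illustration at 46/46.** Fusion in 43/46 v 36/46 gives p = 0.069 (conditional) and 0.047 (Boschloo). These tables were picked to lie between the two cut-offs, so they show the mechanism and not how often it matters.

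**The case against.** The strongest reply is that nothing here is wrong. The named test holds the 5% level, is standard practice, and applies to secondary outcomes. Conditional against unconditional testing is an old debate on which statisticians differ. That stands as far as the label goes: this is an improvement, not an error. It does not remove the gain, because Boschloo's test gives up no control of the 5% level.

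A second reply is that 46/46 is special. It is the planned number for the NDI at one year. Fusion is read at 6 months, operative complications will be known for nearly all 100 patients, and loss to follow-up rarely leaves exactly equal arms. This also stands. A reader might infer from the 46/46 figures that every yes/no outcome runs at 2-3% and loses 6-12 points. The documents do not support that: neither the split nor the rates are fixed, the level is lower for rare outcomes, the maximum level rises to about 4% with unequal arms, and the loss for fusion-type rates is then often only a few points. With full data at 50/50 the gain is 5.5 points for 90 v 70 and 6.3 for 90 v 75.

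Third, the test's label is not defined, and a fuller protocol or analysis plan may define it. The conditional reading is the natural one but is not certain.

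Fourth, better power is not adequate power. For 2 v 10 it does not exceed about 0.4 with either test in the splits tried.

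**Conclusion.** The point holds as a cheap improvement for secondary outcomes. At 46 per arm the conditional test runs at a true level of about 2-3% for common rates of 10-90% and about 0.6% at 5% or 95%. It costs about 4-12 points of power against Boschloo's test. With slightly unequal arms the cost is about 1-8 points for fusion-type rates and about 5-13 for rare events. In every scenario and split tried, Boschloo's test had the higher power.

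This rests on the conditional reading of the named test, on two-sided alpha 0.05, and on assumed rates. A reader might go further and infer that the planned test is invalid or that the trial's conclusions are at risk. Neither follows: the test errs on the safe side, and the NDI equivalence comparison and the sample size do not use it.

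**What to change.** Before the 1-year data are analysed, name Boschloo's unconditional exact test for all two-arm yes/no outcomes: fusion, subsidence above 3 mm, radiolucency, good result on perceived recovery, reoperation and complications. Keep the exact Pearson test for outcomes with more than two categories, because Boschloo's test as used here is for 2 x 2 tables only. State the significance level and that the tests are two-sided. Fixing this in advance matters because a choice between the two tests made after seeing a table such as 43/46 v 36/46 would follow the result.

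The cost is a line or two of wording. The test is in standard software and needs no extra patients or data. The downside is that it is less familiar to readers; a one-sentence explanation in the report would cover that.

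### The NDI comparison is planned as a t-test on change; adjusting for the baseline NDI already collected would usually give a tighter interval at no data cost

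*Protocol article*

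**What the plan says.** All statements are in the protocol article.

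- **Test.** Sample size and data analysis: "Parametric data will be evaluated using the Student’s t-test". The sentence is general. It does not name the NDI and mentions no covariate.
- **Equivalence criterion.** Same section: "The two groups will be considered equivalent if the mean NDI improvement for the silicon nitride cage group is within a range" of the PEEK mean plus or minus the MCID. The quantity compared is therefore change from the pre-operative score.
- **Second NDI analysis.** Same section: "A repeated measurements analysis of variance for the primary outcome measure will also be performed in order to compare the evolving patterns over time". This comes in addition and describes time courses; it does not supply the equivalence estimate.
- **Sizing.** Same section: the assumed change is "10% reduction (improvement) with a standard deviation of 22" per cent, and the margin is given as "The Minimal Clinically Important Difference (MCID) for the NDI is 7.5 points or 15% [31], which is the equivalence interval for sample size calculation". The result is "A 46-patient Valeo C enrollment has a power of .90 when compared with a PEEK study arm of the same size", raised to 100 in total for 8% loss.
- **Data available.** Outcome assessment, Table 2: the row "Neck Disability Index, Arm Pain VAS, Neck Pain VAS, SF-36, Recovery Likert" is marked pre-operatively and at 3, 6, 12 and 24 months.

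**The concern.** Subtracting the baseline score fixes its coefficient at 1. Unless that happens to be the true regression slope, change remains correlated with baseline. Two things follow. The variance of the treatment difference is larger than it need be, and a chance difference in baseline NDI between two arms of about 46 passes in part into the realised estimate.

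Precision matters more than usual here. An equivalence claim is best supported when the whole confidence interval lies inside the margin, so the width of the interval drives the chance of success. Enrolment leaves no reserve against the trial's own 90% target: 100 less 8% is 92, which is exactly 46 per arm. The covariate that would narrow the interval is already on the visit schedule.

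**Working it through.** **Inputs from the protocol article:** SD of NDI change 22%; margin 15% (7.5 of 50 points); 46 evaluable per arm; power 0.90; 8% loss; total 100. Alpha and confidence level are not stated, so both common choices are shown. The true difference is taken as 0.

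**Step 1. Reproduce the plan's figure.**

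SE = 22 × √(2/46) = 4.59 percentage points.

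Power of two one-sided tests (TOST), normal approximation: 2Φ(15/SE − z) − 1.

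- One-sided 0.05 (90% interval): 15/4.59 = 3.27; 3.27 − 1.645 = 1.625; power 0.896. With the t distribution, 0.890.
- One-sided 0.025 (95% interval): 3.27 − 1.96 = 1.31; power 0.810. With the t distribution, 0.798.
- A standard two-sided 0.05 difference formula gives n = 46 and power 0.905.
- Enrolment: 92/0.92 = 100.

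The stated 0.90 with 46 per arm is reproduced at one-sided 0.05, using the SD of change. The plan is thus sized for an unadjusted comparison of change, and that comparison delivers about what is promised.

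**Step 2. Effect of baseline adjustment with equal variances.**

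Let r be the correlation between baseline and 12-month NDI, and let both have variance s².

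- Change score: variance 2s²(1 − r).
- ANCOVA residual: variance s²(1 − r²).
- Ratio: (1 − r²)/(2(1 − r)) = (1 + r)/2.

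The documents do not give r, so 0.3 to 0.7 is assumed, with the SD of change held at 22%. Residual SD = 22 × √((1 + r)/2). Power uses the t distribution, 46 per arm:

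| Analysis | SD (%) | SE (%) | Power, 90% interval | Power, 95% interval |
|---|---|---|---|---|
| t-test on change | 22.0 | 4.59 | 0.89 | 0.80 |
| ANCOVA, r = 0.3 | 17.7 | 3.70 | 0.98 | 0.96 |
| ANCOVA, r = 0.5 | 19.1 | 3.97 | 0.96 | 0.92 |
| ANCOVA, r = 0.7 | 20.3 | 4.23 | 0.94 | 0.88 |

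**Step 3. Exposure to chance imbalance.**

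Under the same assumptions the slope of change on baseline has size 1 − r, and the baseline SD is 22/√(2(1 − r)). A baseline difference of one standard error therefore shifts the expected difference in change by 22 × √((1 − r)/2) × √(2/46). This is 2.7 percentage points at r = 0.3 and 1.8 at r = 0.7, against a margin of 15.

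**Step 4. Relax the equal-variance assumption.**

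Let k be the 12-month SD divided by the baseline SD. The ratio of ANCOVA to change-score variance becomes k²(1 − r²)/(1 + k² − 2rk). The gain is zero when rk = 1.

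- r = 0.7, k = 1.4: 1.96 × 0.51/(1 + 1.96 − 1.96) = 1.00, so no gain.
- r = 0.3, k = 1.4: 1.96 × 0.91/(1 + 1.96 − 0.84) = 0.84, against 0.65 at k = 1.
- r = 0.5, k = 0.8: 0.64 × 0.75/(1 + 0.64 − 0.80) = 0.57, against 0.75 at k = 1.

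The powers in Step 2 are therefore illustrations for k = 1, not bounds.

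**The case against.** The strongest reply is that nothing here is wrong. The compared quantity is improvement, so baseline already enters by subtraction. The sample size uses the SD of that same quantity, and Step 1 shows that the planned test reaches about the stated power. This stands: the point is one of efficiency, not validity.

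A reader might infer that the t-test gives a biased result. The documents do not support that. Allocation is randomised with sealed envelopes, so the difference in change is unbiased over randomisations, and the variability due to chance imbalance is already counted in the 22% SD. Step 3 concerns only the single realised estimate, given the imbalance that occurred.

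A reader might also infer that the trial is underpowered. Power falls to about 0.80 only if equivalence is judged on a 95% interval, and the article states no such level. As worded, its rule compares means without mentioning an interval.

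Finally, covariates are often left to an analysis plan, which is not shown, and the t-test sentence is general. This stands in part: that the analysis is unadjusted is partly inferred from silence. But the t-test is the only two-group test named that fits the NDI criterion, and it cannot carry a covariate. An analysis plan that adjusted for baseline would depart from the published sentence.

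**Conclusion.** The point holds as a free improvement. The planned t-test on change is valid and delivers about 0.89 to 0.90 power at one-sided 0.05. Baseline adjustment would generally be more precise and would protect the realised estimate from chance imbalance.

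With equal variances and r between 0.3 and 0.7, the variance falls by 15% to 35% (1 − 0.85 to 1 − 0.65). The main uncertainty is the size of the gain: neither r nor the ratio of the two SDs is in the documents. The gain is larger if the 12-month SD is the smaller one. It shrinks as that SD rises above the baseline SD, and reaches zero when r times the SD ratio equals 1.

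**What to change.** In Sample size and data analysis, state before the data are analysed that:

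- the primary treatment difference and its confidence interval come from an ANCOVA of 12-month NDI on treatment and baseline NDI;
- that interval, at a stated confidence level, is judged against ±7.5 points;
- the t-test on change is kept as a sensitivity analysis;
- VAS and SF-36 are analysed in the same form, each with its own baseline.

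A term for operating surgeon is optional. The described randomisation is not stratified by surgeon, and none of the figures above depends on such a term.

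The cost is a sentence or two of wording. No new data, visits or patients are needed, and the sample size can stay as it is. Fixing the model in advance also rules out a later choice between adjusted and unadjusted results.
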